## Abstract

**Background:**

Inadequate preoperative patient preparation causes organizational, economic, and emotional problems to patients and professionals. In Spain, no current evidence is available on either the rate of compliance or the impact of good compliance with preoperative recommendations by patients in the ambulatory setting. However, it is known that around 25% of surgical cancellations in the major ambulatory surgery (MAS) are due to poor compliance with these recommendations and, therefore, avoidable. Introducing innovative tools based on mobile health (mHealth) apps may help patients meet the preoperative recommendations and, consequently, reduce the rate of cancellations in the ambulatory setting.

**Objective:**

The objective of this study was to evaluate the effectiveness of the Listeo+ mHealth app as a tool for improving compliance with preoperative recommendations in MAS versus standard of care (SOC).

**Methods:**

A multicenter, randomized, open-label clinical trial that compares SOC with the additional use of Listeo+, a specific mHealth app for MAS preoperative patient monitoring, is being conducted. The study will include patients aged ≥18 years with surgical indication for MAS who meet the necessary technological and connectivity requirements. Patients in the control group will receive written preoperative recommendations, while those in the intervention group will additionally use the Listeo+ mHealth app. There will be a competitive recruitment of 790 patients during 6 months in 4 hospitals in Andalusia (Spain) that belong to the National Health System. The primary efficacy outcome is the level of compliance with preoperative recommendations. Secondary outcomes include the rate of cancellations, associated resource consumption, and perceived usability and utility with Listeo+ by participants of the intervention group. Simple randomization 1:1 procedure will be used to allocate patients to each study group.

**Results:**

The technological development of Listeo+ and the integration and interoperability of information systems was completed in September 2017. Subsequently, simulation tests were performed with Listeo+, and a pilot study was initiated with real patients that concluded successfully in October 2017. Patient recruitment began in December 2017 in the 4 participating centers. After an intermediate analysis performed 10 months after the start of the recruitment phase, the data collection and cleaning phases are estimated to be completed in April 2019, and the analysis with the final results will be conducted in July 2019.

**Conclusions:**

Progress in the integration and interoperability of information systems represents a major step forward in the field of mHealth. The app will allow health professionals to monitor in real-time patients’ preparation and critical preoperative recommendations fulfillment. We expect a reduction in avoidable preoperative cancellations due to a lack of or a poor patient preparation. Self-assessed Web-based questionnaires and focus group will provide important information about the perceived usability and utility of Listeo+ app among patients and health care professionals.

**International Registered Report Identifier (IRRID):**

DERR1-10.2196/10938

## Introduction

Providing quality care in different phases of the surgical process has become an important challenge for health systems because of the increase in the care burden, the increase in the complexity of surgical procedures, and increasingly demanding attention focused on patients’ preferences [1]. Throughout the surgical process, different factors (organizational, relative to patients’ clinical condition, or medical) can lead to surgery cancellations or surgical delay [2-4]. The implications of surgery cancellations can be analyzed from the perspectives of health management and patient safety, as their effects on health resource consumption can be considered adverse events (AEs) that require control and monitoring [5-7]. One major cause is the inadequate preoperative patient preparation because the safety guarantees for the intervention are not met [8,9]; this affects both the quality of the surgical procedure and the consumption of hospital resources as a result of the increase in hospital stay and consumption of medicines [1].

Major ambulatory surgery (MAS) is characterized by short-term postoperative care and does not require hospital admission; it has greatly increased in developed countries in recent decades [10]. In Spain, it represents 62.5% of the total number of surgeries performed by the National Health System (NHS) [11], which is one of the highest rates among Organisation for Economic Co-Operation and Development member countries [12]. Although the rate of cancellations in MAS is approximately 4% [13,14], lower than that reported in other countries where cancellations on the day of surgery oscillate between 5% and 40% [10,15], a quarter (27%) of those cancellations are because of poor compliance with preoperative recommendations and are, therefore, avoidable [13,16]. Conversely, inadequate preoperative patient preparation for MAS is also considered one of the main causes of patient no-shows on the day of surgery [17], which is likely due to patient anxiety before surgery [18].

There are tools such as preassessment clinics (PACs) and the surgical safety checklist (SSC) that help minimize risks in the preoperative process by assessing patients’ anesthetic risk [19] or verifying compliance with essential surgical aspects from the beginning to the end of surgery [20]. Regarding these two elements, one of the initiatives to ensure that the requirements established in the preoperative assessment are met is to provide recommendations to patients so they can participate in their own care in aspects such as the use of medications (eg, anticoagulants and biologicals) and hygienic and dietetic measures. In this way, we hypothesize that involving patients in the preoperative care and promoting them to meet the specific recommendations can lead to avoiding risky situations and, consequently, surgery cancellations.

Currently, there is evidence of the benefits of PACs and the SSC on the reduction of postoperative complications in the ambulatory setting [21], preoperative anxiety [18], and cancellations for medical reasons (eg, inappropriate use of medication before surgery) [22,23].

Some experiences based on information and communication technologies, such as incorporating the SSC in digital form to the electronic health record (EHR) or sending short message service text messages as a reminder of health appointments, have made it possible to increase compliance to treatment and surgical recommendations, reduce cancellations, and avoid no-shows [1,24-27]. Currently, mobile devices (tablet, mobile phone, and wearable devices) have a very high degree of penetration in Spain [28], Andalusia in particular, with 70.9% of the population (some 4.8 million inhabitants) connecting to the internet through these devices [29]. Because of its characteristics, (eg, mobility, instant access, connectivity, and variety of functionalities), mobile health (mHealth) can influence patients’ attitudes and behaviors and facilitate the asynchronous information exchange between patients and health professionals [30]. Some mHealth-based interventions such as the use of mHealth apps, have proven effective in the management of chronic diseases (eg, diabetes, asthma, and hypertension) by improving clinical parameters, compliance, and reducing disease costs [31]. Despite their great potential, the few initiatives undertaken thus far in the ambulatory surgical setting have been limited to postoperative patient monitoring [32,33]. Thus, there is no available evidence of the effect of mHealth apps on compliance with preoperative recommendations and, consequently, on the reduction of surgical cancellations.

Listeo+ is a multifunctional mobile app that provides personalized information to surgical patients (date and time of surgery), adjusted to their clinical condition. In addition to sending reminders on critical aspects of the operation at different times, Listeo+ monitors compliance with preoperative recommendations by establishing a communication channel between patients and health care professionals, which facilitates intervention in the case of possible AEs.

The aim of this study is to evaluate the impact of Listeo+ as a complement to standard of care (SOC) in patient compliance with preoperative recommendations, surgery cancellations, and associated resource consumption in the ambulatory surgical setting, in a clinical context of real-world evidence, and to evaluate the user experience with the app (perceived usability and utility).

## Methods

### Study Design

A multicenter, randomized, and open-label controlled trial was planned to evaluate the Listeo+ mHealth app as a complement to SOC in patients undergoing MAS. The study protocol has two arms: patients who receive preoperative written recommendations (control group) and patients who use the Listeo+ mHealth app as a multifunctional tool to monitor personal recommendations from health professionals (intervention group). The study considers guidelines and recommendations of the Standard Protocol Items: Recommendations for Interventional Trials [34] and Consolidated Standards of Reporting Trials statements [35].

The study protocol has been approved in a peer-review process by the Spanish Ministry of Economy and Competitiveness in its Technological Projects in Health call on July 14, 2015 (application identification DTS15/00228) and by the Andalusian Regional Ministry of Health in its Health Research Projects call on July 15, 2015 (application identification PI-0447-2014).

### Study Setting

Four High-Resolution Hospital Centers belonging to the Public Health System of Andalusia as a part of the NHS hospital network are recruiting patients for this study (Multimedia Appendix 1). High-Resolution Hospital Centers encourage ambulatory surgery and short-term hospitalization using MAS; thus, they were considered suitable centers to evaluate the initiative. Participating Hospital reference population is about 187,957 inhabitants.

### Eligibility Criteria

#### Characteristics and Selection Criteria of Patients Undergoing Major Ambulatory Surgery

Patients participating in this study will be adults aged ≥18 years at the start of the study who will undergo MAS in the specialties of traumatology, orthopedic surgery, ophthalmology, or general surgery.

#### Inclusion Criteria

To participate in this study, participants should be autonomous or dependent on one or more caregivers to perform their preoperative preparation, with the necessary technological and connectivity resources (ie, to dispose a smartphone or tablet mobile device with an Android or iOS operating system with an internet connection and familiarity with mobile technologies).

Patients who are autonomous to perform their preoperative preparation and lack the technological requirements but have caregivers with the necessary technological and connectivity resources who can supervise their preoperative preparation may also be included in the study.

#### Exclusion Criteria

Patients with two scheduled operations during the same clinical episode or time period will be excluded from the study. Nonautonomous patients, whose caregivers cannot be located when personal preoperative recommendations (Multimedia Appendix 2) are provided, and patients of the intervention group who have not downloaded and registered on Listeo+ will also be excluded. To avoid the loss of patients, a rescue procedure will be used with patients who, within 7-14 days, have not registered on the Listeo+ app. A telephone call will be made urging them to register on the Listeo+ app. If a patient has not registered within 72 hours (3 days) after the rescue call has been made, he or she will be excluded from the study.

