### Sample Size and Statistical Plan

The sample size required to estimate the main objective of this study was calculated as 395 patients per group for a total of 790 patients. This estimate was made assuming an alpha risk of .05, a beta risk of .2, and a difference in proportions between the groups of 10%. The analysis will be performed considering per intention-to-treat (ITT) and per protocol populations. The ITT population will include all randomized patients, whereas the per protocol population will include randomized patients who finally obtain an appointment to undergo MAS.

In addition, statistical analyses will be performed using the R software version 3.3.2 (R Foundation for Statistical Computing). For all analyses, an alpha risk of .05 will be assumed; therefore, to consider a statistically significant difference, the *P* value of the contrast statistic should be ≤.05. The statistical analysis planned *a priori* will consist of a descriptive analysis of the demographic and clinical characteristics of patients. For quantitative variables, the mean, SD, 95% CIs, variance, SE, 5% trimmed mean, median, minimum, and maximum will be calculated. For qualitative variables, frequency distributions with their respective percentages will be calculated. To determine whether there are differences in the level of compliance with surgical recommendations between the group with written recommendations and the group with written recommendations plus the app, Fisher's exact test will be performed.

To assess the influence of sociodemographic and clinical characteristics of patients in the level of compliance with preoperative recommendations, multivariate logistic regression will be performed. Furthermore, the reasons for the exclusion of the ITT population will be included.

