### Allocation

Patients who meet the inclusion criteria and sign informed consent will be provided with an information sheet about the project and evaluated before participating in the study. To allocate patients to study groups, simple randomization 1:1 procedure will be used. To include patients in the study, each center will be provided with one randomization scheme generated by computer. Given the characteristics of the study, it is not possible to blind patients and professionals. Subsequently, we will collect sociodemographic data (age, sex, area of residence of patients, level of education of patients or caregivers using the app or patient or caregiver of the control group, occupation, marital status, and knowledge or handling of apps), clinical data (type of surgery, medical diagnosis [International Classification of Diseases, Ninth Revision], anesthetic evaluation, and medications taken), and functional situation by measuring disability (Barthel index).

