### Ethical Aspects of the Study, Confidentiality, and Privacy

The study protocol has been evaluated and approved by the Regional Ethics Committee of Andalusia through the Biomedical Research Ethics Portal of Andalucía (PEIBA, for its acronym in Spanish). This study will be conducted in accordance with the principles of the latest version of the Declaration of Helsinki and will follow the Good Clinical Practice guidelines of Spain.

Written informed consent duly signed by all patients, legal representatives, or caregivers participating in this study will be collected before patient allocation to study groups. Data confidentiality will be protected under the Spanish law that ensures the protection of personal data (Organic Law on Protection of Personal Data, 15/1999, December 13). The researcher of each center will be responsible for keeping a study file containing patient identification and information, including the informed consent form signed by patients. Throughout the study, all related documents will be located in a secure area of the participating center. Any analysis derived from the study will be performed from an anonymized database; it will not contain any identification of patients or caregivers but only a numeric code, through which it will not be possible to reveal their identities. At the end of the study, the researcher will be responsible for preserving the necessary documentation for at least 5 years.

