## Results

Currently, this study is in the recruitment phase, which will end once 790 patients are included (395 for each arm). The data collection and cleaning phases are estimated to be completed in April 2019, and the analysis with the final results will be conducted in July 2019.

Previously, the technical aspects of interoperability between the hospital and the Listeo+ app backend (set of system components accessible only to the developers or platform administrators) were resolved successfully, defining an application programming interface for Web services. In December 2016, an eCRF was created that was fully integrated into the EHR of the participating centers.

Prior to the recruitment of patients, a pilot phase was conducted in January 2017 with the aim of identifying complications in the subsequent phases of recruitment and data analysis. During the pilot phase, face-to-face sessions were held in the hospitals with both health professionals and specialized information and communication technologies personnel. In these sessions, test runs were performed with several patients, verifying the effective communication between the systems and the usability of the new functionality integrated into the EHR. As a result, a telephone call was included in the protocol, at 7 and 14 days after the provision of recommendations during the anesthesiologist appointment, for the patients of the intervention group who had not downloaded their personal preoperative recommendations using the QR code. In addition, two new recommendations were added (see Multimedia Appendix 2: R1_18 and R3_24), and the wording of the recommendations was modified to facilitate patient understanding. Simultaneously, improvements were made in the design and functionality of Listeo+.

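### Intervention patients who do not register on Listeo+ are removed after randomisation, with no counterpart among controls, which contradicts the ITT definition and can bias the comparison

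*Protocol article*

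**What the plan says.** The rule stands in the protocol article under Exclusion Criteria: "patients of the intervention group who have not downloaded and registered on Listeo+ will also be excluded". A rescue call precedes it, and then: "If a patient has not registered within 72 hours (3 days) after the rescue call has been made, he or she will be excluded from". What the patient leaves, in that sentence, is the study itself. The Intervention section gives app access to intervention patients. The Participants section sends controls along the usual route with written recommendations and sets them no comparable test. On timing, the ethics section says that written consent "will be collected before patient allocation to study groups", and Allocation says that a "simple randomization 1:1 procedure will be used".

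Sample Size and Statistical Plan defines two analysis sets. For the first, "The ITT population will include all randomized patients". For the second, "the per protocol population will include randomized patients who finally obtain an appointment to undergo MAS". The same section adds that "the reasons for the exclusion of the ITT population will be included".

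**The concern.** Membership of the intervention group exists only once a patient has been allocated, so failing to register is behaviour after randomisation, although it is listed as an eligibility criterion. Controls who would have failed to register cannot be identified and stay in. The arms are then no longer the groups that randomisation formed.

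The primary outcome is itself compliance with instructions. The rule removes people who did not act on an instruction even after a call urging them to, and such people may well comply less with preoperative recommendations too. If so, the app can look effective when it does nothing. The Introduction promises evidence from a real-world context, but followed as written the rule compares app registrants with all controls. The cancellation outcome is exposed in the same way.

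**Working it through.** **Step 1: set the rules side by side.** Take a patient allocated to Listeo+ who does not register within 72 hours of the call. Exclusion Criteria puts this patient out of the study. The ITT definition keeps the patient in. The per protocol definition asks only for a surgical appointment and is silent on registration, so it gives no reason to drop the patient either. The promise to report reasons for exclusion from the ITT population implies exclusions from a set defined as everyone randomised. No section says whether outcomes of excluded patients are still collected.

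**Step 2: the plan's own figure.** The article gives 395 per group for alpha .05, beta .2 and a 10-point difference in proportions, with no base rate. With p̄ the mean of the two proportions,

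n = [1.96√(2p̄(1−p̄)) + 0.842√(p₁(1−p₁)+p₂(1−p₂))]² / (p₂−p₁)².

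- 50% v 60%: 387.3, so 388.
- 45% v 55%: 391.3, so 392.

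The stated 395 is within 3% of both, so it fits a two-sided test with a base rate near 50%. The sample size is not in dispute here.

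**Step 3: size of the bias.** Let f be the share of the intervention arm excluded and g the mean compliance of registrants minus that of non-registrants. Suppose that the app has no effect. The control mean is then that of the full mix, m_reg − f·g, and the retained intervention mean is m_reg. The spurious difference is f × g. The article gives neither quantity, so these pairs are assumptions:

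- 10% × 10 points = 1 point
- 20% × 15 points = 3 points
- 20% × 20 points = 4 points

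With g = 0 the bias is 0. With g negative the sign reverses: 20% × −10 points = −2 points.

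**Step 4: chance of falsely favouring the app.** The nominal chance in that direction is 2.5%. The article describes the outcome as an average percentage but plans a difference in proportions with Fisher's exact test, so both scales are shown (normal approximation).

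- Mean scale: SE = SD × √(1/395 + 1/(395(1−f))), and the chance is Φ(bias/SE − 1.96). No SD is given, so 20, 30 and 40 points are assumed. At SD 20, SE is 1.462 for f = 10% and 1.509 for f = 20%. It scales in proportion to the SD.
- Proportion scale, base rate 50% assumed: SE is about 3.66 points for f = 10% and 3.77 for f = 20%.

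| Scale | Bias 1 point | Bias 3 points | Bias 4 points |
|---|---|---|---|
| Mean, SD 20 | 10.1% | 51.1% | 75.5% |
| Mean, SD 30 | 6.6% | 26.3% | 42.3% |
| Mean, SD 40 | 5.3% | 16.7% | 26.3% |
| Proportion, base 50% | 4.6% | 12.2% | 18.4% |

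Example: 4/1.509 = 2.65, and Φ(2.65 − 1.96) = 75.5%.

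**Step 5: power if everyone is kept.** Assume a 10-point effect in registrants, none in non-registrants and a base rate of 50%. The effect is 10 × (1−f), and power at 395 per arm is Φ((d − 1.96·s₀)/s₁), with s₀ the pooled and s₁ the unpooled standard error.

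- f = 0: d = 10, power 80.8%.
- f = 10%: d = 9, (9 − 1.96 × 3.543)/3.529 = 0.58, power 72%. For 80%, 480 per arm.
- f = 20%: d = 8, (8 − 1.96 × 3.546)/3.535 = 0.30, power 62%. For 80%, 609 per arm.

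**The case against.** The best defence of the text is that exclusion means only removal from the per protocol set. The wording does not allow this: the removal is from the study, and the per protocol definition does not mention registration. Nor is this a detail left to an unseen analysis plan, because two stated rules conflict. Which analysis set leads is commonly settled there, and its absence is not held against the article.

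Other objections limit how far the point goes, and they stand:

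- **Direction.** A reader might infer that the trial is certainly biased toward Listeo+. The article reports no compliance by registration status, so the direction is an inference. Both arms must already have a device, a connection and familiarity with the technology, or a caregiver with the means. That may limit non-registration and any gap.
- **Lost outcomes.** A reader might infer that nothing is recorded for excluded patients. The article does not say so. The eCRF sits inside the EHR, so the data may exist.
- **Frequency.** The Results section says that a call was added after the pilot "for the patients of the intervention group who had not downloaded their personal preoperative recommendations using the QR code". A reader might take this as evidence of substantial non-registration, but the pilot is described as test runs with several patients and no rate is given.
- **Size.** The larger false-positive figures depend on an assumed SD of 20. For the same 4-point bias the chance falls from 75.5% to 18.4% on the proportion scale.
- **Rescue call.** Exclusion Criteria speaks of non-registration within 7-14 days, Results of a call at 7 and 14 days for non-download. These can be read as one procedure, so this is a point of wording and not a contradiction.

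**Conclusion.** The exclusion rule is wrong as written. It removes randomised patients from one arm for post-allocation behaviour and cannot be applied together with an ITT set of all randomised patients. That conclusion rests on the text alone.

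The bias is conditional. If non-registrants comply less, the comparison favours the app by about the share excluded times the gap: 1 to 4 points under the assumed pairs, against a design difference of 10. The chance of a false finding for the app rises from 2.5% to between 4.6% and 75.5% across the scales and spreads tried. The shares, gaps, SDs and base rate are all assumptions, and the article offers no way to check them. Because the flaw affects the randomised comparison on the primary outcome, it needs correcting before the final analysis.

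**What to change.** - Delete the non-registration exclusion and the rule that takes a patient out of the study 72 hours after the call. The call itself can stay.
- Keep every randomised patient in the ITT set as allocated, and score compliance and cancellations at the existing checkpoints (anaesthesia consultation, reception on the day of surgery) whether or not the patient registered.
- Draw the main conclusion from ITT. Use registration only to define a per protocol or complier analysis, labelled as supplementary.
- For patients already excluded, retrieve outcomes from the EHR/eCRF where consent allows, and report how many there were.
- Align the wording of the rescue call in Exclusion Criteria and Results.

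Scoring needs no new procedure, but recruitment is under way, so this is an amendment to a running trial. The statistical cost should be stated openly: the effect is diluted. If the app does nothing in non-registrants, power at 395 per arm is about 72% with 10% non-registration and 62% with 20%. The sponsor should either accept that or reconsider the sample size once the non-registration rate is known.
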